Several studies tried to identify determinants for RRIs. One of the reasons that the most important risk factors for RRIs have not yet been identified might be related to the often-underpowered studies performed. Since the development of an RRI results from a complex interaction between both intrinsic and extrinsic risk factors, a multivariate analysis is essential for identifying risk factors for RRIs [10,11]. Multivariate methods are susceptible to producing problematic results if too few RRIs are available relative to the number of risk factors analyzed in the model. As a result, several studies that used this type of analysis first examined the independent link of potential risk factors with RRIs and only factors univariately associated with an RRI were entered into the multivariate model [7,12-14]. To account for the multifactorial nature of RRIs this univariate selection of potential risk factors is undesirable [15]. A large cohort study would increase the number of factors that can be entered into a multivariate model and therefore reduce the need for a univariate selection, hence it is needed for identification of risk factors for general and specific RRIs which is important for the development of preventive measures.

The primary objectives of the NLstart2run study are therefore to determine short- and long-term health effects of a nationwide “Start to Run” program and to identify determinants for RRIs in novice runners. This information is important for developing successful running promotion programs in the future [16]. Secondary objectives are to determine reasons and determinants for dropout from a supervised running promotion program, and to identify the course and medical consumption of injured runners and the associated costs. In this article we describe the protocol of the prospective cohort study NLstart2run.

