## Methods/design

### Study design

The NLstart2run study is a multi-center prospective cohort study with a follow-up at 6, 12, 24 and 52 weeks, as can be seen in Figure 1. The study design, procedures and informed consent procedure were approved by the Medical Ethics Committee (no. 2012/350) of the University Medical Center Groningen (UMCG), the Netherlands. The trial is registered in the Netherlands Trial Registry (NTR3676).

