### Study population

All participants that sign up for the 6-week Start to Run (STR) program of the Dutch Athletics Federation in 2013 will be asked to participate in the NLstart2run study. The STR course is organized twice a year and starts in March and September. The STR participants will be recruited by the Dutch Athletics Federation via national and local media. Additional information about the study and procedures is sent to all STR participants. Participants can register for the study after signing a digital informed consent.

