#### ***Inclusion & exclusion criteria***

Participants of the STR program who are aged between 18 and 65 are eligible for inclusion. Participants will be excluded if there are absolute contraindications for vigorous physical activities according to the American College of Sports Medicine ACSM) guidelines [17], or in case of unwillingness to keep a running log.

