#### ***Follow-up questionnaires***

The runners starting with the STR program in March 2013 will receive four follow-up questionnaires at 6, 12, 26 and 52 weeks after beginning with the program. The group of runners who start in September will only receive three follow-up questionnaires at 6, 12 and 26 weeks. In the follow-up questionnaires continuation and reasons for discontinuation of running will be monitored. Participation in other sports will also be monitored in the follow-up questionnaires. Besides questions about continuation of running or other sport activities, all follow-up questionnaires also measure physical activity (SQUASH), motivation toward exercise (BREQ-2), and physical and mental health (RAND-36, 7-items scale of Pearlin and Schooler, 5-item scale on high prevalent health complaints, and shortened 6-item scale for loneliness).

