### Statistical analyses

Incidence of RRIs will be calculated for all participants and for male and female participants separately as the number of new injuries reported per 1000 hours of running exposure. Exposure time (in hours of running exposure) will be calculated from the time the participant started the running program until an RRI is reported (injured runners) or until the end of the program (non-injured runners).

Descriptive data will be presented as means (± s.d.) and frequency distributions.

For identification of risk factors for RRIs only data from the baseline questionnaire and the running log will be used. Data of the follow-up questionnaires will not be used for this purpose, because these data do not contribute to a pre-running risk-profile. It is possible for a single subject to sustain multiple RRIs during the study period. In this case only the occurrence of the first RRI will be used for analysis. Potential risk factors for RRI will be entered into a multivariate Cox regression prediction model. Hazard ratios and the corresponding 95% confidence intervals will be calculated for the factors associated with RRI.

Data of the baseline and follow-up questionnaires will be compared with a repeated-measures ANOVA to examine the health effects of participating in a supervised running program. Reasons for dropout from the start-to-run program will be described and determinants for dropout will be analyzed by multivariate logistic regression models. Course and medical consumption and the associated direct and indirect costs will be described for injured runners.

Missing data will be completed by multiple imputation using the Multiple Imputation by Chained Equations (MICE) procedure, a technique in which missing values are replaced based on estimated relations in the dataset [37]. Ten multiple imputed datasets are generated, whereupon the results of those ten multiple imputed datasets will be combined using the rules given by Rubin [37].

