## Discussion

The extensive baseline questionnaire and follow-up questionnaires will provide insight into the short- and long-term health effects of participation in a 6-week running promotion program. Perceived health, physical activity in daily life and motivation to exercise will be monitored over time and thereby describe the effects of a running program for novice runners. Sports participation during and after the 6-week STR course will be monitored. Reasons and determinants for discontinuation for both running and sports will be examined as well. These findings may reduce dropout rates from future running or sports promotion programs and increase adherence to sports during and after a program.

The NLstart2run study will result in several leads for future RRI prevention programs. The large sample size and the extensive baseline measurements will result in ample information on determinants for RRIs in novice runners. As a result of the large group of participants, it will be possible to study risk factors for specific RRIs or in specific subgroups. These findings will result in new information regarding modifiable risk factors that can be applied in future running promotion programs to minimize dropout due to injury.

As a result of the NLstart2run study, valuable information on health effects and RRI prevention for novice runners will be gained. Moreover, medical consumption and consequences of an RRI, as well as reasons and determinants for discontinuation and dropout from a running promotion program will be examined. This information can be used for the implementation of more effective running promotion programs, thus making a positive contribution to public health.

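### Health effects of the program are read from before-after change in one fully exposed cohort, which cannot separate the program from season, secular trend or the timing of sign-up

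*Protocol article*

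**What the plan says.** The first primary objective, in the Background, is to "determine short- and long-term health effects of a nationwide “Start to Run” program". Under Study design, the study is a single prospective cohort. Under Study population, recruitment is confined to people entering the program: "All participants that sign up for the 6-week Start to Run (STR) program of the Dutch Athletics Federation in 2013 will be asked to participate". No waiting-list, non-participant or other comparison group is described.

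The section Statistical analyses gives the method for this objective in one sentence: baseline and follow-up questionnaires are "compared with a repeated-measures ANOVA to examine the health effects of participating in a supervised running program". The Discussion says that monitoring the measures over time will "thereby describe the effects of a running program for novice runners". No caution about reading the change causally is stated.

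On timing, Study population says: "The STR course is organized twice a year and starts in March and September". According to Follow-up questionnaires, the March wave "will receive four follow-up questionnaires at 6, 12, 26 and 52 weeks after beginning with the program", while the September wave has questionnaires at 6, 12 and 26 weeks only. Statistical analyses adds that missing data will be completed by chained-equations multiple imputation with ten data sets.

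**The concern.** In a cohort where everyone is exposed, mean change from baseline is the sum of any program effect, seasonal movement, secular trend and whatever follows from the moment at which people choose to enrol. The planned comparison estimates the sum. The article fixes both the method and the inference drawn from it, so this is not a detail left to a fuller document.

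Season deserves attention because one outcome is habitual physical activity in an ordinary week (SQUASH), which could plausibly vary over the year, and because the two waves go through their early follow-up in opposite halves of the year. The week-52 occasion exists for one wave only, so a time profile drawn across all occasions describes a different group at its last point.

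At stake is what can be concluded on a primary objective: that the program improved health, or that participants' scores changed during and after it.

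**Working it through.** **1. The plan's own figure.** Sample size: 6,000 × (1 − 0.20) = 4,800 at follow-up; 4,800 × 0.20 = 960 injuries; 960 / 10 = 96 model terms. These figures reproduce, but they concern the injury objective. None is given for health effects. I take 4,800 as the number of baseline/follow-up pairs.

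**2. Smallest mean change that reaches significance.** Assumed, since the article gives neither: two-sided 5% level and within-person correlation r of 0.5 to 0.7. In SD units, SE = √(2(1 − r)/n), and the threshold is 1.96 × SE.

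| n | r | SE | Threshold (SD) |
|---|---|---|---|
| 4,800 | 0.5 | 0.0144 | 0.028 |
| 4,800 | 0.7 | 0.0112 | 0.022 |
| 2,400 | 0.5 | 0.0204 | 0.040 |
| 2,400 | 0.7 | 0.0158 | 0.031 |

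The 2,400 rows assume an even split into waves, which the article does not state.

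**3. Chance that a non-program shift is significant.** With no program effect, a shift b and n = 4,800, the probability is Φ(b/SE − 1.96) + Φ(−b/SE − 1.96).
- b = 0.05 SD: b/SE is 3.46 (r = 0.5) or 4.47 (r = 0.7), giving 0.93 or 0.99.
- b = 0.02 SD: 0.28 or 0.43.

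**4. Season, as an illustration.** Assumed: an annual cosine with amplitude 0.1 SD peaking in mid-July, s(w) = 0.1 × cos(2π(w − 28)/52), with starts in calendar weeks 11 and 37. The change at week t is s(start + t) − s(start). The starts are 26 weeks apart, so the September change is minus the March change. With a share p of March starters, the pooled change is (2p − 1) times the March change.

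| Week | March wave | September wave | Pooled 50:50 | Pooled 60:40 | Pooled 70:30 |
|---|---|---|---|---|---|
| 6 | +0.070 | −0.070 | 0 | +0.014 | +0.028 |
| 12 | +0.129 | −0.129 | 0 | +0.026 | +0.052 |
| 26 | +0.093 | −0.093 | 0 | +0.019 | +0.037 |
| 52 | 0 | no questionnaire | – | – | – |

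The amplitude is not from the article, and the shifts scale in proportion to it. The week-12 value at 60:40 lies within the threshold range of step 2. At 70:30, weeks 12 and 26 exceed the range and week 6 sits at its upper end.

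**5. Week 52.** If all available responses are averaged, the week-26 mean is p × M + (1 − p) × S, where M and S are the March and September means, and the week-52 mean comes from March starters alone. Even with no change in either wave, the profile would step by (1 − p)(M − S). For example, p = 0.5 and an assumed wave difference of 0.1 SD give 0.5 × 0.1 = 0.05 SD. If week 52 is imputed for September starters instead, no September starter is observed at that occasion, so the values rest entirely on March starters. The article does not say which route is meant.

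**The case against.** The strongest reply is that much of what a reader might infer goes beyond the text.

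- **The waves are pooled without a wave term.** This is inferred from silence. One sentence in a condensed article lists no model terms, and a full analysis plan may contain them. The reply stands: the absence of the term from the article is not itself a fault.
- **Pooling creates the seasonal bias.** It does not. Drifts of waves six months apart have opposite signs and tend to cancel, completely so for a symmetric cycle at a 50:50 split. Week 52 against baseline is March against March. Seasonal exposure is therefore limited to weeks 6, 12 and 26, when the waves are unequal or when one wave is read alone.
- **Regression to the mean will be reported as benefit.** It is possible if people enrol at a low point. However, the eligibility text sets no cut-off on a health or activity score ("Participants of the STR program who are aged between 18 and 65 are eligible for inclusion", with exclusions for contraindications and for unwillingness to keep a log), and nothing in the article allows its size to be derived.
- **The thresholds show bias.** They do not. Any large study detects small shifts. They show only that a significant result will not discriminate between explanations.

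None of this supplies a comparator. Cancelling season would remove one alternative explanation and leave secular trend and sign-up timing in place.

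**Conclusion.** The point holds in a limited form. The stated analysis of a primary objective measures change in participants, while the article calls that change the health effects of participating. Without a comparator, the change cannot be separated from season, secular trend or the timing of sign-up, and it may be reported as a program effect. The documents do not establish that it will be misreported, or by how much.

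For scale, 0.022 to 0.028 SD is enough for significance with 4,800 pairs, given r between 0.5 and 0.7 and a 5% level. The seasonal figures are illustrations that rest on an assumed amplitude, peak and wave split. The week-52 composition change needs no assumption, since it follows from the questionnaire schedule; its size depends on how far the waves differ.

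**What to change.** 1. Word the objective and the conclusion as change during and after the program in participants, and state the lack of a control group as a limitation.
2. Add start wave and wave-by-time to the repeated-measures model and report change separately by wave.
3. Restrict the week-52 contrast to March starters. State that September starters' week-52 values are absent by design and will not be imputed.
4. Optionally, compare March starters at week 26 with September starters at baseline, adjusted for age, sex, BMI and prior sport, as a same-season sensitivity check only. It does not remove regression to the mean, because the September baseline is taken at sign-up. It does not remove selective response, because it sets those still answering at week 26 against new enrolees. It says nothing about weeks 6 and 12.

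Study design gives the third follow-up differently ("The NLstart2run study is a multi-center prospective cohort study with a follow-up at 6, 12, 24 and 52 weeks") from Follow-up questionnaires, which has week 26. The two should be reconciled; the working above uses 26.

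The cost is slightly more analysis on data already to be collected, and a more cautious conclusion.

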### Sample size

Based on previous studies on RRIs among novice runners, an injury incidence of 20% is expected [7,14,18]. Taking into account a dropout rate of 20% [6,7,14,18,19], the inclusion of 6,000 participants will lead to approximately 4,800 participants at follow-up. With an RRI incidence of 20%, a total of 960 RRIs are expected. Taking into account the need of a minimum of 10 RRIs per risk factor analyzed in a multivariate model, this is sufficient for accounting for the multivariate nature of RRIs [15,20].

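### The number of imputations is fixed at ten whatever the amount of missing data; tying it to the observed missingness would steady borderline results at no cost beyond computing time

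*Protocol article*

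**What the plan says.** The Statistical analyses section of the protocol article sets one method for all missing data: "Missing data will be completed by multiple imputation using the Multiple Imputation by Chained Equations (MICE) procedure". It then fixes the number: "Ten multiple imputed datasets are generated", and "the results of those ten multiple imputed datasets will be combined using the rules given by Rubin". It gives no reason for ten and no provision for more if missingness turns out larger.

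The Sample size section expects losses: "the inclusion of 6,000 participants will lead to approximately 4,800 participants at follow-up". It continues: "With an RRI incidence of 20%, a total of 960 RRIs are expected". Both figures serve to size the study; neither is linked to the imputation.

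Two analyses that serve the primary objectives would use the imputed data: a repeated-measures ANOVA of the baseline and follow-up questionnaires, and a multivariate Cox model for running-related injury (RRI) that draws only on baseline and running-log data. For the latter, "Hazard ratios and the corresponding 95% confidence intervals will be calculated". No significance level is stated.

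**The concern.** A pooled result from a finite number of imputations carries simulation noise: repeat the imputation with another random seed and the estimate, its standard error and its p-value move. The size of that movement depends on how much information is missing, so a number chosen before the missingness is known may be ample or thin.

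With 20% dropout expected over several questionnaire waves and many log rounds, it is reasonable to ask whether ten is enough for the health outcomes. For the injury model, the protocol's own requirement is "the need of a minimum of 10 RRIs per risk factor analyzed in a multivariate model", so 960 expected events would allow up to 960/10 = 96 factors. Among many factors some are likely to lie near whatever limit readers apply, and those could look associated in one run and not in another.

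**Working it through.** **Inputs from the protocol article.** m = 10, pooled by Rubin's rules (Statistical analyses). 6,000 included, 20% dropout, 20% injury incidence (Sample size). These reproduce the plan's figures: 6,000 × (1 − 0.20) = 4,800, and 4,800 × 0.20 = 960.

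**Assumptions.** FMI is not in the document and is taken from 0.05 to 0.5. The limit of 1.96 (two-sided 0.05) is inferred from the 95% intervals.

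**Formulas.**
- Relative efficiency = 1/(1 + FMI/m).
- Monte Carlo error of the pooled estimate, as a share of its standard error = sqrt(FMI/m).
- Chance that a result whose noise-free z is 2.1 falls below 1.96 in one run = Φ(−0.14 / sqrt(FMI/m)), holding the standard error fixed.

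The last three columns use the rule m = 100 × FMI, never below ten.

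| FMI | Efficiency, m = 10 | Error/SE, m = 10 | z = 2.1 falls below 1.96, m = 10 | m by rule | Error/SE by rule | Falls below 1.96 by rule |
|---|---|---|---|---|---|---|
| 0.05 | 0.995 | 0.071 | 2% | 10 | 0.071 | 2% |
| 0.10 | 0.990 | 0.100 | 8% | 10 | 0.100 | 8% |
| 0.20 | 0.980 | 0.141 | 16% | 20 | 0.100 | 8% |
| 0.30 | 0.971 | 0.173 | 21% | 30 | 0.100 | 8% |
| 0.50 | 0.952 | 0.224 | 27% | 50 | 0.100 | 8% |

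The rule caps the error at 10% because sqrt(FMI/(100 × FMI)) = 0.10.

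**Simulation.** The closed form leaves out the variation of the pooled standard error and the degrees of freedom. A simulation of 200,000 draws per setting included both. Below, *limit p* is the p-value that an unlimited number of imputations would give.

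- FMI 0.20, limit p 0.05: the central 95% of p-values over seeds runs from 0.023 to 0.109 at m = 10, 0.029 to 0.086 at m = 20 and 0.036 to 0.070 at m = 50.
- The same at m = 10 for other FMI: 0.036 to 0.071 (FMI 0.05), 0.030 to 0.084 (0.10), 0.018 to 0.135 (0.30), 0.014 to 0.159 (0.40).
- FMI 0.20, m = 10, chance that one run gives p < 0.05: 99.9%, 96%, 85% and 65% for limit p of 0.01, 0.02, 0.03 and 0.04; 27%, 8% and 2% for limit p of 0.06, 0.08 and 0.10. The unstable band is therefore roughly 0.02 to 0.10.
- FMI 0.20, limit p 0.03: two seeds disagree about p < 0.05 in 26% of pairs at m = 10, 11% at m = 20 and 0.8% at m = 50.

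The closed form is the milder of the two. For limit p 0.03 (z = 2.17) it gives Φ(−0.21/0.141) = 7% of runs above 0.05, against 15% in the simulation.

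**The case against.** The best defence is that ten imputations are a sound choice and that what remains is tuning. Much of this stands.

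- **Validity.** At FMI 0.20 the efficiency is 0.980 and the standard error is inflated by about 1%. Rubin's rules already carry the finite-m noise into the pooled variance and degrees of freedom. Estimates and intervals are not biased.
- **Dropout is not FMI.** A reader might equate the 20% with an FMI of 0.20. The protocol does not support that. In a Cox model a participant who drops out is ordinarily censored, so FMI for a hazard ratio comes from missing baseline and log items, about which nothing is said. For the questionnaires the link is closer, but FMI still varies by wave and with how well observed scores predict missing ones. At 0.05 to 0.10 ten is already adequate by the rule above.
- **Consequence.** A reader might also infer that the primary results could not be reproduced. Only borderline results are affected. With 4,800 people, z = 2.1 for a within-person change is 2.1/sqrt(4,800) = 0.03 standard deviations of the change score, too small for crossing 1.96 to alter a conclusion about health in the whole cohort.
- **Any finite number has this property.** At limit p 0.05 two seeds disagree about half the time even with m = 100. More imputations narrow the unstable band; they do not remove it.
- **No cut-off is stated.** The plan reports hazard ratios with intervals and gives no p-value rule for listing factors.

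What survives is narrower: the protocol commits to a number that cannot respond to the missingness actually found, when a rule that can respond costs almost nothing.

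**Conclusion.** The point holds as a free improvement. The plan is not wrong to use ten imputations; it is needlessly rigid in fixing ten before the missingness is known.

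If FMI is about 0.2 or more, Monte Carlo error is at least 14% of the standard error, and at FMI 0.2 results with p of roughly 0.02 to 0.10 may change on re-imputation. At FMI 0.05 to 0.10 the error is 7 to 10%, and little would be gained. The case is most direct for the repeated-measures health outcomes and conditional for the Cox model.

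The conclusion rests on an assumed FMI and on a 0.05 limit that the 95% intervals only imply. One might argue for a high FMI because the September starters receive no 52-week questionnaire (Follow-up questionnaires section), but the protocol does not say that this wave would be imputed for them, so it cannot be counted as evidence.

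**What to change.** In Statistical analyses, replace the fixed ten with a rule tied to the observed missingness. For example: the number of imputed datasets will be at least 100 times the largest FMI among the parameters of interest, or at least the percentage of incomplete records, and never fewer than ten.

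At FMI 0.20 this means 20 datasets and at 0.50 it means 50, holding Monte Carlo error at 10% of the standard error and efficiency at 1/(1 + 0.01) = 0.99. The FMI can be estimated from a first run of ten.

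The cost is computing time only: no further data, participants or design change. Fixing the seed and reporting the Monte Carlo error would go well with it, but such details commonly belong in the analysis plan, and their absence here is not a fault.
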